#### Study procedure

2.5.4

The participants will not be informed of their groups. After the initial assessment at baseline, the control group will receive usual care, whereas the interventional group will be provided with the structured intervention. A qualified pharmacist (researcher) will educate the patients in the interventional group about disease (diabetes), its symptoms, clinical goals, self-care activities (self-monitoring of blood glucose, physical activity, importance of regular medication in-take and healthy diet), and reducing risks, whereas the control group patients (N = 40) will receive the usual care.

The pharmacist will provide face-to-face diabetes management education (approximately 30 minutes duration) to the patients in the intervention group at their first visit, follow-up visit (12th week), and 4 telephone (4th, 8th, 16th, and 20th week) and will recommend physician visits when necessary. In addition to face-to-face educational intervention patients in the intervention group will also be provided informatory brochures about self-care activities, and a log book to keep record of their self-monitored blood glucose levels. The educational intervention and patient informatory material has been designed according to American diabetes Association (ADA) guidelines, the details of are presented in Table 1.

**Table 1 T1:**
[figure not shown]
Module for educational intervention.

Details about patients’ (intervention and control group) demographics and lab profile (HbA1c, random blood sugar, fastening blood sugar, etc.) will be obtained by the pharmacist at first visit. At baseline and end of the trail (24th week), the diabetes disease knowledge and self-care activities of the patients in both groups (intervention and control) will be assessed by using 2 prevalidated questionnaires in Urdu language [24-item Urdu version of DKQ and 16-item Urdu version of DSMQ]. Pharmacists can assist the patient in completing questionnaires, but will not provide any help in answering the questions, as the same questionnaires will be used repeatedly. The details of study schedule for data collection are presented in Table 2.

**Table 2 T2:**
[figure not shown]
Study schedule for data collection for intervention and control groups.

### Measurement tools

2.6

#### Diabetes knowledge score

2.6.1

DKQ, developed for the Starr County Diabetes Education Study, has been translated and validated in Urdu language in Pakistan.^[29]^ DKQ is a 24-item questionnaire. The DKQ scoring involves summing up the scores of all the correct items of each participant, where higher score will indicate better patient's diabetes knowledge. One point will be given to each correct answer and no point for the incorrect option.

#### Self-care practices

2.6.2

DSMQ will be used to measure the patient's self-care activities. DMSQ was originally developed to evaluate diabetes self-care behaviors associated with glycemic control within common therapeutic options for adult patients of type 1 and type 2 DM.^[30]^ Respondents will be asked to rate their specific self-care activities of last 3 months on a 16-item DSMQ. This questionnaire involves a four point likert scale (ranging from 0 – ‘does not apply to me’ to 3 – ‘applies to me very much’). There are 4 subscales of this study tool; namely, ‘Glucose Management’ (GM), which is comprised of 5 statements: 1, 4, 6, 10, 12, ‘Dietary Control’ (DC): comprised of 4 statements: 2, 5, 9, 13, ‘Physical Activity’ (PA): comprised of 3 statements: 8, 11, 15, and, ‘Health-Care Use’ (HU): comprised of 3 statements: 3, 7, 14. The last item (item 16) asks the respondents to rate their overall diabetes self-care, hence its score is included only in the ‘Sum Scale’ (summation of all of the 16 items).

The scoring process of the DSMQ involves, adding up the scores of all 16 items after reversing the scores of 9 negatively keyed statements. Higher scores will represent more effective self-care. Finally DSMQ scores will be transformed to a scale ranging from 0 to 10, where a score of 10 will indicate the most effective self-care behavior.

#### Statistical methods

2.6.3

The analyses will be performed using SPSS 22.0.0 (SPSS Inc., Chicago, IL, USA). Frequencies and descriptive statistics will be used for patients’ demographic presentation, while means and standard deviations will be calculated for the continuous variables and group differences will be analyzed by using Pearson chi-square test for categorical variables. Kolmogorov-Smirnov test will be applied to check the distribution of data. Independent *t* test will be used in case of normally distributed data, whereas, Mann–Whitney *U* test for non-normal distributions. Primary outcomes of the educational intervention, which are changes in HbA1C levels, self-care activities scores (DSMQ) and disease knowledge scores (DKQ) will be analyzed by using one-way analysis of variance (ANOVA) for normally distributed data and Kruskal Wallis Test for non-normally distributed data. *P* < 0.05 will be considered as significant for all analysis.

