**Results::**

The primary outcome is change in patients’ HbA1c, whereas, changes in self-care activities and patients’ disease knowledge are the secondary outcomes. After baseline assessment of their self-care activities and disease knowledge by using validated Urdu versions of Diabetes Self-management Questionnaire (DSMQ) and Diabetes Knowledge Questionnaire (DKQ), respectively, interventional group patients will be supplemented with a face-to-face pharmacist-led educational intervention, whereas, the control group will receive usual care. Intervention arm patients will be educated successively at their first follow-up visit (12th week) and telephonically after every 4 weeks. All assessments will be made at baseline and end of trail for both intervention and control groups. Multivariate general linear model will be applied to analyze the effects of the intervention.

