Educational interventions can play an important role to improve patients’ knowledge and skills regarding diabetes self-management. Systematic reviews of interventions addressing diabetes self-management indicate that the diabetes education courses enhance knowledge, self-care behaviors, and reduction in HbA1C.^[13–16]^ Structured self-management education programmes can be delivered on a one-to-one basis or to groups of people with diabetes and should be facilitated by trained educators. The aim of the education is not only to improve knowledge and skills, but also to motivate a person to make and sustain lifestyle changes, by giving them the confidence to make their own treatment/lifestyle choices on a day-to-day basis.

Educational intervention on self-management can be delivered as group education or individually as one-to-one approach. Sturt et al. reported that an individualized approach with the help of a diabetes guide and telephonic support has demonstrated clinically significant reductions in A1c levels, for T2DM patients with poor glycemic control.^[17]^ Health literacy has been reported as a significant factor influencing the patients’ glycemic control.^[18]^ Clinical outcome can be achieved by addressing patients’ literacy. Pharmacist-based educational interventions are associated with improved medication adherence and glycemic control.^[19–21]^ A review of 16 pharmacist-based interventions resulted in an absolute reduction of HbA1c with an average of 0.62%.^[20]^ Similarly, in an another review, a reduction in A1c levels up to 2.1% was demonstrated by 20 pharmacist-based interventions.^[13]^ A study examining the effectiveness of a free rural clinic for diabetes patients managed by pharmacists found that patients who received education on diabetes, lifestyle modifications, and management of diabetes drug therapy had significant reductions in A1c (≥ 1%) after 24 months.^[22]^

Keeping in view the importance educational interventions in diabetes self-care and clinical outcomes, we designed a face-to-face short-term (6 months) pharmacist-led educational intervention model in poorly controlled T2DM patient (HbA1c >7%) in Pakistan. In this study, we will investigate the mean change in HbA1C at 6 months after the baseline, and a comparison will be made with a similar comparator group of T2DM patients receiving standard diabetes care. In addition, comparison between self-care activities and disease knowledge between the groups will also be studied.

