#### Sample size calculations

2.5.3

Study sample size is calculated based on previous studies ^[23–28]^ for detecting the difference of 1% reduction for HbA1C (effect size) with standard deviation of 1.4%, at 6 months in the intervention group. A significance level of 0.05 is considered with study power of 80%. Based on these numbers, the calculated sample size is 62 (31 for experimental group and 31 for controlled group); however, a sample of 80 patients is assumed to be sufficient to compensate for a 25% attrition rate.

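### The primary HbA1c analysis is not uniquely fixed: the abstract and section 2.6.3 name different methods, and 2.6.3 lets a normality test choose between a mean-based and a rank-based test

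*Protocol article*

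**What the plan says.** Two places in the protocol article describe how the intervention effect will be analysed.

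- **Abstract, Results paragraph:** "Multivariate general linear model will be applied to analyze the effects of the intervention". The same paragraph fixes the hierarchy: "The primary outcome is change in patients’ HbA1c, whereas, changes in self-care activities and patients’ disease knowledge are the secondary outcomes".
- **Section 2.6.3, Statistical methods:** "Kolmogorov-Smirnov test will be applied to check the distribution of data". An independent t "test will be used in case of normally distributed data, whereas" Mann-Whitney covers the non-normal case; no outcome is attached to that pair. The changes in HbA1c, DSMQ and DKQ "will be analyzed by using one-way analysis of variance (ANOVA) for normally distributed data and Kruskal Wallis Test for non-normally distributed data".

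Two other places show what the trial wants to estimate. The Introduction says "we will investigate the mean change in HbA1C at 6 months after the baseline", to be compared with the standard-care group. Section 2.5.3 sizes the trial "for detecting the difference of 1% reduction for HbA1C (effect size) with standard deviation of 1.4"%.

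**The concern.** The abstract's model does not appear in the methods section, and the methods section's tests do not appear in the abstract. The headline test of a multivariate model over several outcomes is a joint test, whereas the abstract and section 2.5.1 make HbA1c alone primary. Within 2.6.3, the choice between ANOVA and Kruskal-Wallis is left to the trial data. The variable to be checked (raw values, change or residuals), the significance level, the version of the test, and whether the arms are pooled are all unstated.

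The two branches do not answer the same question. ANOVA compares means. Kruskal-Wallis compares rank distributions and gives neither a difference in mean HbA1c nor an interval for it. A trial planned around a 1% mean difference could thus report a primary p-value with no prespecified estimate of that difference. Two methods in print also leave room to choose between them once results are known.

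**Working it through.** **1. The sample size is a calculation for means.** Inputs from section 2.5.3: difference 1%, SD 1.4%, significance level 0.05, power 80%. Two-sided testing is assumed.

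n per arm = 2 × (1.960 + 0.842)² × 1.4² / 1² = 2 × 7.85 × 1.96 = 30.8, so 31 per arm and 62 in total. This is the stated figure. One-sided testing would give 25 per arm and does not match. The exact t-based solution is 31.8, so 32 per arm.

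**2. Which named methods really differ.** With two arms, one-way ANOVA is the t test, and Kruskal-Wallis is Mann-Whitney without continuity correction. In one simulated data set at 31 per arm, p = 0.00623 for both members of the first pair and 0.00830 for both members of the second. That leaves two real conflicts: multivariate against univariate, and mean-based against rank-based.

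**3. How often the pretest would select the rank test.** The article gives none of the inputs needed, so these are assumptions: 30 per arm (80 × 0.75 = 60 completers), pretest level 0.05, no true difference, 2000 runs per shape. Each cell shows pooled data / either arm flagged. Lilliefors is the Kolmogorov-Smirnov test corrected for estimating the mean and SD; the ordinary version plugs them in without correction.

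| Assumed shape | Lilliefors | Ordinary K-S |
|---|---|---|
| Normal | 3.3% / 9.4% | 0% / 0.05% |
| t with 5 df | 20% / 28% | 1.6% / 1.2% |
| Gamma(16), skewness 0.5 | 14% / 19% | – |
| Gamma(4), skewness 1 | 43% / 46% | 2.6% / 1.6% |

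A repeat run under skewness 1 gave 40-45% and 1-2%. Pooling also matters when there is a real effect: at 31 per arm with a true 1% difference and skewness 1, Lilliefors flags 31% when pooled and 47% when either arm counts.

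**4. What the choice does to the result.** 31 per arm, SD 1.4%, 3000 runs per scenario, Lilliefors in each arm. The two-stage procedure uses the rank test if either arm is flagged.

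| Assumed shape | Type I error, two-stage | Power: t | Power: rank | t and rank disagree (true 1% difference) |
|---|---|---|---|---|
| Normal | 4.3% | 78.7% | 77.1% | 5.2% |
| t with 5 df | 4.8% | 79.7% | 85.8% | 8.9% |
| Gamma(4) | 5.3% | 79.2% | 83.6% | 7.8% |
| Lognormal (sigma 0.5) | 5.7% | 79.7% | 91.7% | 12.7% |

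**5. Effect of fixing a mean-based test.** At 31 per arm, power is 80.3% by normal approximation and 79.0% by the exact t calculation. The planned number does not change.

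**The case against.** The strongest reply is that little goes wrong in practice. One-way ANOVA is itself a general linear model, and multivariate output usually includes a separate test for each outcome, so the two descriptions may have been meant to overlap. The two-stage procedure holds its error rate. Under skewed or heavy-tailed shapes the rank test has more power than the t test, so the switch can help. Section 2.6.3 also promises means and standard deviations for continuous variables, from which a mean difference could be computed. A full protocol or analysis plan may already name one model.

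Much of this stands, and it rules out several stronger readings that a reader might infer.

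- **Inflated type I error.** The simulated range of 4.3-5.7% does not support it.
- **The choice of test is close to a coin-flip.** This needs both the Lilliefors version and skewness near 1. The article states neither, and gives no figure on the shape of HbA1c change.
- **The t test conflicts with ANOVA, or Mann-Whitney with Kruskal-Wallis.** With two arms this is redundancy. The t/Mann-Whitney sentence may also concern baseline comparisons only.
- **ANOVA across arm-by-visit cells would treat paired values as independent.** Section 2.6.3 analyses changes, which are one value per patient.
- **All mean information is lost on the rank branch.** Arm means and SDs remain as descriptive results.

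The reply does not remove the contradiction. A multivariate model and a rank test are not two descriptions of one analysis, and the article does not say that a per-outcome follow-up test is the primary result. An unseen document could settle the matter, but the two statements here would still disagree. A gain in power does not make the rank test an estimate of the mean difference.

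**Conclusion.** The point holds as a contradiction and a badly fixed rule. The abstract and section 2.6.3 give different analyses for the primary outcome, and 2.6.3 lets a loosely specified normality check choose between tests of different quantities. What is lost on the rank branch is a prespecified between-arm estimate of the 1% difference for which the trial was sized.

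The contradiction is certain from the text. That the check applies to the HbA1c change is the plain reading rather than an explicit statement: no other normality check is named, and the choice of test turns on normality. The size of the harm is uncertain. The switch to ranks could happen in almost no trials or in nearly half, depending on the variant and shape assumed. Disagreement on significance, where a true 1% difference exists, is about 5-13% across the shapes tried. The harm is an undetermined primary estimator and room to choose between two published methods. It is worth correcting but not fatal to the design.

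A neighbouring inconsistency should be settled in the same edit but is a separate matter: section 2.6.3 refers to "Primary outcomes of the educational intervention, which are changes in HbA1C levels, self-care activities scores (DSMQ) and disease knowledge scores (DKQ"), whereas the abstract makes HbA1c the only primary outcome.

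**What to change.** In both the abstract and section 2.6.3, name one primary analysis: a univariate linear model for HbA1c, reporting the between-arm mean difference and its 95% CI whatever a normality test shows. Week-24 HbA1c adjusted for baseline is preferable, because section 2.5.4 already collects HbA1c at the first visit. Delete the rule that switches tests on normality, and drop the word multivariate for the primary outcome. Keep the rank test, or a bootstrap CI for the mean difference, as a prespecified sensitivity analysis. Settle this before outcome data are examined.

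The change is one of wording. It needs no further patients or measurements, and the calculated 31 per arm stands. The small downside is that, with extreme outliers, the rank test has only a sensitivity role.

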#### Primary aim

2.5.1

To investigate the effectiveness of a pharmacist-delivered diabetes management educational program on glycemic control (HbA1c) after completion of intervention (24th week).

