#### Secondary aim

2.5.2

To examine the impact of a pharmacist-delivered diabetes management educational program on self-care behaviors and patients’ diabetes knowledge, by using Urdu versions of 24-item Diabetes knowledge Questionnaire (DKQ) and 16-item Diabetes Self-management Questionnaire (DSMQ).

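### Section 2.6.3 names HbA1c, DSMQ and DKQ all as primary outcomes at P < 0.05, contradicting the abstract, the aims and the sample size, which make HbA1c the only primary outcome

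*Protocol article*

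**What the plan says.** The article defines the primary outcome in two ways.

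- **Abstract, Results:** "The primary outcome is change in patients’ HbA1c, whereas, changes in self-care activities and patients’ disease knowledge are the secondary outcomes".
- **2.5.1 Primary aim:** the effect of the programme "on glycemic control (HbA1c) after completion of intervention (24th week" is the only item listed.
- **2.5.2 Secondary aim:** "To examine the impact of a pharmacist-delivered diabetes management educational program on self-care behaviors and patients’ diabetes knowledge", measured with the DKQ and the DSMQ.
- **2.5.3 Sample size calculations:** the only inputs are an HbA1c difference of 1%, a standard deviation of 1.4%, a significance level of 0.05 and 80% power, giving 31 per group. Neither questionnaire enters the calculation.
- **2.6.3 Statistical methods:** "Primary outcomes of the educational intervention, which are changes in HbA1C levels, self-care activities scores (DSMQ) and disease knowledge scores (DKQ") are to be analysed by one-way ANOVA or the Kruskal-Wallis test, and a P value below "0.05 will be considered as significant for all analysis".

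No section gives a success rule, an order of testing or an adjustment for several primary outcomes.

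**The concern.** The primary outcome decides what the trial can conclude. Here an analyst who follows 2.6.3 gives three outcomes equal rank, and one who follows the abstract and the aims gives HbA1c sole rank. Each could claim to have kept to the protocol.

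The choice matters because the results may well diverge. Section 2.5.4 has the pharmacist teach the disease and self-care content that the DKQ and DSMQ measure, so scores could improve while HbA1c does not. Under the abstract and aims that is a negative primary result with supportive secondary findings. Under 2.6.3 it could be presented as a positive primary result.

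This is not detail that a condensed article leaves to a fuller document. It is one item stated twice, in incompatible terms, and a separate analysis plan could follow either statement.

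**Working it through.** **1. Which definition does the design fit?** Inputs from 2.5.3: difference 1, SD 1.4, significance level 0.05, power 0.80; allocation is 1:1 (2.4). The article does not say whether the test is one- or two-sided.

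n per group = 2 × SD² × (z for alpha + z for power)² / difference²

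- Two-sided: 2 × 1.96 × (1.960 + 0.842)² / 1 = 30.8, so 31 per group and 62 in total. This reproduces the stated figure. (The SD squared, 1.4², is 1.96.)
- One-sided: 25 per group, which does not match.
- Power at 31 per group by the same normal approximation: 80.3%.

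The stated 62 is therefore the size for one primary outcome, HbA1c, at two-sided 0.05.

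**2. What three primary outcomes at 0.05 would imply.** Assume that success on any one outcome counts and that all three null hypotheses are true.

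- Independent outcomes: 1 − 0.95³ = 0.143, or 14.3%. The upper bound without any assumption on correlation is 3 × 0.05 = 15%.
- Correlated outcomes: the article gives no correlations, so these are assumptions. Simulation of three equally correlated normal test statistics (1,000,000 draws) gives:

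| Assumed correlation | At least one two-sided P < 0.05 | At least one significant in favour of the intervention |
|---|---|---|
| 0 | 14.3% | 7.3% |
| 0.3 | 13.6% | 6.8% |
| 0.5 | 12.5% | 6.3% |
| 0.8 | 9.9% | 4.9% |

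The comparators for a single primary outcome are 5% (two-sided) and 2.5% (in favour of the intervention). Even at a correlation of 0.8 the rate is about double.

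**3. Could the trial support three primary outcomes with an adjustment?** With Bonferroni, alpha is 0.05/3 = 0.0167 for each outcome, with z = 2.394.

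- n per group for HbA1c = 2 × 1.96 × (2.394 + 0.842)² = 41.0, rounded up to 42, so 84 evaluable patients. The plan recruits 80 before any attrition.
- At 31 per group, HbA1c power falls from 80.3% to 66.2%.

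The planned sample fits the single-primary definition and not an adjusted three-outcome one.

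**The case against.** The strongest reply is that 2.6.3 is the outlier and may be loose wording. The abstract, both aims, the introduction's closing paragraph and the sample size all point to HbA1c. Nothing says that the statistical section takes precedence, and under the dominant reading the primary type I error stays at 5%. All of that is fair. It shows which statement should be corrected; it does not remove the conflict.

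Several stronger readings are tempting, and the article does not support them.

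- *That the trial plans to claim success on any one outcome.* No success rule is stated. The Discussion hypothesises improvement in HbA1c, self-care and knowledge together; read as requiring all three, that would not inflate type I error. The most that can be said is that nothing prevents an any-one claim.
- *That the error could reach 30% by counting the four DSMQ subscales as well* (1 − 0.95⁷ = 0.302). Section 2.6.2 describes the subscales as part of the instrument, but 2.6.3 plans no subscale tests. The sum score also cannot be independent of its own components.
- *That DKQ and DSMQ are both unblinded self-report.* The DKQ is scored on correct answers (2.6.1), so it is a knowledge test. Participant blinding is itself stated inconsistently: 2.1 calls the trial open label, while 2.5.4 says that participants will not be told their group.
- *That 14.3% measures the likely harm.* A real gain in knowledge is a true effect, not a false positive. The figure applies only when all three nulls are true. The other risk, a true gain on a secondary measure presented as the primary result, is one of labelling and has no such number.

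The abstract also mentions a multivariate general linear model, which could mean a joint test of the three outcomes. That does not resolve the matter, because 2.6.3 specifies ANOVA or Kruskal-Wallis and the abstract itself keeps HbA1c as sole primary.

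**Conclusion.** Wrong as written. Section 2.6.3 contradicts the abstract, sections 2.5.1 and 2.5.2, and the basis of the sample size in 2.5.3. The contradiction is on the face of the article and depends on no assumption.

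Its consequence is conditional. With no success rule or adjustment stated, 2.6.3 leaves room to report a DSMQ or DKQ finding as a positive primary result. If any one success counted and all nulls were true, the family-wise error would be 14.3% under independence and about 10% to 14% at assumed correlations of 0.8 to 0.3, against 5%. If HbA1c is held as the sole primary outcome, the error stays at 5% and the calculated 62 evaluable patients stands. This should be settled before analysis, because it determines what the trial may conclude.

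**What to change.** Change 2.6.3 so that it says, in substance: *the primary outcome is change in HbA1c from baseline to week 24, tested at two-sided 0.05; changes in DSMQ and DKQ scores are secondary outcomes; the trial's primary conclusion rests on HbA1c alone.* This keeps change in HbA1c as the outcome and brings 2.6.3 into line with the abstract, the aims and the sample size.

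The cost is a sentence or two of wording, with no new data, no extra patients and no change to the sample-size calculation. The one small loss is that a DSMQ or DKQ result can no longer be claimed as primary. How the secondary outcomes are ordered or adjusted among themselves can be left to the analysis plan and is not needed to remove the contradiction.

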### Sample recruitment procedures

2.4

Patients will be identified from the hospital record and who will meet the inclusion criteria of the study will be invited telephonically for participation in the study. If the patient is willing to participate in the study, an appointment will be set in the outpatient counselling room of the pharmacist at CDA hospital and purpose of the study will be explained to the patient and his/her written informed consent will be obtained and baseline assessments will be done. Simple random sampling technique will be used from a list of random numbers of eligible patients which will be compiled by using the patients’ hospital identification numbers. After recruitment, the patients will be requested to handpick an envelope from the basket indicating allocation to either control or intervention group with 1:1 randomization. AB will generate the random allocation sequences, [name] will enrol participants and HS will assign participants to intervention and control groups.

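### Changes in HbA1c, DSMQ and DKQ are tested without using the baselines collected: a valid test that gives up precision, and one that the abstract's named model does not match

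*Protocol article*

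**What the plan says.** Section 2.6.3 (Statistical methods) takes the changes in HbA1c, DSMQ score and DKQ score as the outcomes and states that they "will be analyzed by using one-way analysis of variance (ANOVA) for normally distributed data and Kruskal Wallis Test for non-normally distributed data". One-way means that treatment group is the only factor, and Kruskal-Wallis has no covariate either.

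The abstract says something else: the intervention's effects will be analysed with a multivariate general linear model. It names no covariate.

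The baseline values exist. Section 2.5.4 (text after Table 1) says that the "lab profile (HbA1c, random blood sugar, fastening blood sugar, etc.) will be obtained by the pharmacist at first visit", for both groups, and that DSMQ and DKQ are completed at baseline and week 24. HbA1c above 7% is an entry criterion (section 2.3).

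Allocation (section 2.4) is by having patients "handpick an envelope from the basket indicating allocation to either control or intervention group with 1:1 randomization"; no stratification on HbA1c is described. Section 2.5.3 bases the sample size on "detecting the difference of 1% reduction for HbA1C (effect size) with standard deviation of 1.4%, at 6 months in the intervention group".

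**The concern.** A change score subtracts the whole baseline value, which is the same as assuming that week-24 HbA1c rises one for one with baseline. Baseline and week-24 values are imperfectly correlated, so with equal SDs the true slope is r, which is below 1. Two things follow.

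- **Precision.** The change score carries baseline noise that a fitted slope would remove.
- **Chance imbalance.** If one arm starts higher by chance, a fraction (1 − slope) of that difference stays in the estimated effect and flatters the arm that started higher.

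The trial randomises 80 patients without described stratification, so some imbalance is to be expected. At stake is the precision of the primary HbA1c comparison and how readily its result can be defended if the arms differ at entry. The two descriptions of the analysis also leave it unclear which model the trial will report.

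**Working it through.** **Inputs from section 2.5.3:** difference 1.0 HbA1c point; SD 1.4; significance level 0.05 (taken as two-sided); power 80%; 31 per arm.

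**Assumptions:** r is not given, so 0.3, 0.5 and 0.7 are shown. The arithmetic covers the ANOVA branch only.

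**1. The plan's own figure.** n per arm = 2 × 1.4² × (1.960 + 0.842)² / 1.0² = 30.8, rounded up to 31, or 62 in total. This matches "the calculated sample size is 62 (31 for experimental group and 31 for controlled group". Power at 31 per arm is 80.3% by the normal approximation and 79.0% by the noncentral t. A one-sided test would need only 25 per arm. The stated size is therefore that of an unadjusted two-group comparison.

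**2. Variance ratio with equal SDs (s) at both times.**
- Var(change) = 2s²(1 − r)
- Var(ANCOVA) = s²(1 − r²)
- Ratio ANCOVA/change = (1 + r)/2 = 0.65, 0.75, 0.85 for r = 0.3, 0.5, 0.7

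**3. Variance ratio if entry narrows the baseline.** As an illustration only, take a bivariate normal population with mean 8 and SD 1.4 at both times, entering only above 7.
- Cut-point: (7 − 8)/1.4 = −0.714. The normal density over the upper tail there is 0.405.
- Share of baseline variance kept: k = 1 − 0.714 × 0.405 − 0.405² = 0.546, so the baseline SD is 1.4 × √0.546 = 1.03.
- Selection on baseline leaves the slope at r and the residual variance at s²(1 − r²). Var(change) becomes s²(1 − r²) + (1 − r)²ks².
- Ratio = (1 + r)/[(1 + r) + (1 − r)k] = 0.77, 0.85, 0.91.

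**4. Power at 31 per arm, equal SDs, noncentral t.**

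| Reading of 1.4% | r | SD of change | Power, change | ANCOVA residual SD | Power, ANCOVA |
|---|---|---|---|---|---|
| SD of week-24 values | 0.3 | 1.66 | 65% | 1.34 | 83% |
| | 0.5 | 1.40 | 79% | 1.21 | 89% |
| | 0.7 | 1.08 | 95% | 1.00 | 97% |
| SD of change | 0.3 | 1.40 | 79% | 1.13 | 93% |
| | 0.5 | 1.40 | 79% | 1.21 | 89% |
| | 0.7 | 1.40 | 79% | 1.29 | 85% |

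On the first reading the SD of change is 1.4√(2(1 − r)), which exceeds 1.4 when r is below 0.5, while the ANCOVA SD, 1.4√(1 − r²), never exceeds 1.4. On the second reading the ANCOVA SD is 1.4√((1 + r)/2), and the planned power does not depend on r.

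**5. Chance imbalance at 31 per arm.**
- With baseline SD 1.4, the SE of the baseline difference is 1.4 × √(2/31) = 0.36, and a gap above 0.5 points has about a 16% chance.
- With the narrowed SD of 1.03, the SE is 0.26 and that chance is about 6% (0.5/0.263 = 1.90 SEs).
- A 0.5-point gap shifts the change-score difference by (1 − r) × 0.5 = 0.25 at r = 0.5, or 0.15 at r = 0.7.
- Given such a gap, type I error with s = 1.4 is about 7.4% (r = 0.5) or 6.6% (r = 0.7). For r = 0.5: critical value 1.96 × 0.356 = 0.697; conditional SE 1.212 × √(2/31) = 0.308; (0.697 − 0.25)/0.308 = 1.45 gives 7.3% in one tail and 0.1% in the other.

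**The case against.** The strongest defence is that the planned test is sound. Averaged over randomisations, a comparison of change scores between arms is unbiased with 5% type I error, and it already removes most of a baseline difference when r is high. A 0.3-point imbalance at r = 0.5 shifts the estimate by 0.5 × 0.3 = 0.15, less than half the SE of the treatment difference, 1.4 × √(2/31) = 0.36. This stands. A reader might infer that the primary analysis is biased or invalid, and the documents do not support that.

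A second defence is that section 2.5.3 does not show a power shortfall. In the wording "with standard deviation of 1.4%, at 6 months in the intervention group", the time point may attach to the reduction and not to the SD. On that reading 1.4% is the SD of change and the stated 62 reproduces. The inference that the trial is underpowered unless r is at least about 0.5 holds only on the other reading, with equal SDs; the text does not settle which is meant.

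Third, the entry threshold might seem to be what pulls the slope below 1. It is not: imperfect correlation does that. Selecting on baseline leaves the slope alone and narrows the baseline SD, which makes both the gain from adjustment and the expected imbalance smaller than the equal-SD figures.

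Finally, the general linear model in the abstract could hold a baseline covariate. It names none, and multivariate ordinarily refers to several outcomes. It does not supply the adjustment, and it conflicts with section 2.6.3.

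**Conclusion.** The point holds as a weakness in efficiency and in conditional behaviour. Section 2.6.3 expressly fixes covariate-free tests, so this is a stated choice and not a detail left to an unseen analysis plan. Under the assumed r of 0.3 to 0.7, ANCOVA would have 15% to 35% less variance with equal SDs, or about 9% to 23% less in the narrowed-baseline illustration. The direction is the same in every case shown. The size rests on a correlation that the documents do not give, on the SD assumptions, and for power on which reading of 1.4% is right. No firm figure for power lost can be stated. The mismatch between the abstract and section 2.6.3 needs no assumption and must be resolved along with it. Making the change is advisable; leaving it would not invalidate the trial.

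**What to change.** In section 2.6.3, prespecify one primary analysis: a linear model (ANCOVA) of week-24 HbA1c on treatment group and baseline HbA1c, reporting the adjusted mean difference with its 95% confidence interval. Analyse DSMQ and DKQ in the same way, each adjusted for its own baseline. Keep the unadjusted comparison of changes as a supporting analysis only. Reword the abstract so that it names this same model. In section 2.5.3, say whether 1.4% is the SD of week-24 HbA1c or of its change.

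The cost is a few sentences before analysis and one degree of freedom per model. The baselines are already collected, SPSS fits the model, and the sample size need not change.
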